### 3. STUDY DESIGN

The study design is an *explorative randomized, placebo-controlled and double-blind intervention crossover study: Transvamix (100mg/mL THC / 50mg/mL CBD) to treat chronic pain in Epidermolysis Bullosa*. For further overview, see Table 1. Sixteen (16) participants will be enrolled for this study.

This is an explorative study because cannabinoid-based medicines (CBMs), Transvamix-like drugs, have not yet been studied by way of controlled trials in the EB patient population.

The addition of placebo mitigates confounding participation bias. The crossover design reduces the number of participants required, an important factor when studying rare diseases, and supported by randomization and blinding, enables rigorous statistical analyses. In addition to this, both intra-participant outcomes as well as group analyses by intervention type can be analysed.

Participants will receive both the IMP (Transvamix) and placebo in forward or reverse orders, depending on treatment arm allocation. The study drugs (Transvamix & placebo) will be provided by Felix Farma, and dispensed by the Transvaal pharmacy. A washout of two weeks between both interventions will mitigate carry-over effects as up to 80-90% of THC is excreted via the urine within 5 days (terminal elimination half life of 21.5 hours), and the elimination half-life of CBD is between 1.44 and 10.86 hours after oromucosal spray administration (5–20 mg). The duration of participation is 9 weeks. All participant reported outcome measurements (PROMs) are completed online, at home.

| Table 1: Table of Study-related Activities for the duration of C4EB |                             |                                    | Until day -8          | Day -7 to -1                                       | Day 1 to 14                                        | Day 15 to 28            | Day 29 to 42                                                   | Day 55                                                                           |
|---------------------------------------------------------------------|-----------------------------|------------------------------------|-----------------------|----------------------------------------------------|----------------------------------------------------|-------------------------|----------------------------------------------------------------|----------------------------------------------------------------------------------|
|                                                                     | Time required               | Location                           | Eligibility Screening | Before intervention with Transvamic-oil or Placebo | Titration and Maintenance of Transvamic or Placebo | Washout Period (no IMP) | (Crossover) Titration and Maintenance of Transvamic or Placebo | Structured interview on study participation, events and feedback on methodology. |
| Eligibility Screening; NRS pain; medication recording               | 60 minutes                  | Video conference / telephone       | Completed             |                                                    |                                                    |                         |                                                                |                                                                                  |
| Transvamic or Placebo administration                                | N/A                         | Administered at home               |                       |                                                    | Administration following titration scheme          |                         | Administration following titration scheme                      |                                                                                  |
| PROM:
*(DN-4; CSI; HADS; PCS; SF-MPQ2; PSEQ)
**( MPQ2; PSEQ)  | *40 minutes
**20 minutes | Online survey completion at home   |                       | (day -1)*                                          | (day 14)**                                         |                         | (day 42)**                                                     |                                                                                  |
| Logbook (VAS Pa/Pr , dose administered, side-effects)               | 10 minutes                  | Online survey completion at home   |                       | (daily)                                            | (daily)                                            |                         | (daily)                                                        |                                                                                  |
| Urine Toxicology                                                    | N/A                         | UMCG dermatology outpatient clinic |                       |                                                    | (day 14)                                           |                         | (day 29)                                                       |                                                                                  |
| fMRI scan Center for Medical Imaging UMCG)                          | 20-30 minutes               | Center for Medical Imaging UMCG    |                       | (day -1)                                           | (day 14)                                           |                         | (day 42)                                                       |                                                                                  |
| Participation time in days (total = 64 days, or 9 weeks and 1 day)  |                             |                                    |                       | 7                                                  | 14                                                 | 14                      | 14                                                             | 14                                                                               |

## 4. STUDY POPULATION

### 4.1 Population (base)

Participants in this study are adult patients with the diagnosis of inherited epidermolysis bullosa (EB) and genetic diagnosis of one of the EB subtypes. All patients with EB in the Netherlands are registered at the Center for Blistering Diseases, Department of Dermatology, UMC Groningen.

In order to participate, patients must currently be living in the Netherlands and be at least 16 years of age. Participation is not limited to one sex, nor to any ethnic group. As of January 2020, 196 patients fulfil the basic demographic criteria for participation (>16 years of age, EB diagnosis, Dutch speaking and living in the Netherlands).

### 4.2 Inclusion criteria

In order to be eligible to participate in this study, a subject must meet all of the following criteria:

- Clinical diagnosis, supplemented by genetic analysis, immunofluorescent diagnostics or electron microscopy of congenital epidermolysis bullosa (EB). Including the subtypes *recessive dystrophic EB*, *dominant dystrophic EB*, *junctional EB* and *EB simplex*.
- At least 16 years of age from the date of onset of participation.
- Can read and write in the Dutch language.
- Mentally competent and legally able to appreciate informed consent.
- Reporting an average pain or pruritus mean score  $\geq 4$  on NRS (0-10) averaged throughout the previous week at one of the following times of day: morning, afternoon or evening.
- Negative COVID-19 testing will be required prior to participation

### 4.3 Exclusion criteria

A potential subject who meets any of the following criteria will be excluded from participation in this study:

- Patients enrolled in other clinical trials that do not allow for a deviation in treatment.
- Have experienced myocardial infarction or clinically significant cardiac dysfunction within the last 12 months or have had a cardiac disorder that, in the opinion of the investigator would have put the participant at risk of a clinically significant arrhythmia or myocardial infarction.

- Patients with known psychotic disorder (including the use of antipsychotic medications), or a history of suicidal ideation.
- Female patients of child-bearing potential and male participants whose partner was of child-bearing potential, unless willing to ensure that they or their partner used effective contraception.
- Patients who have had significantly impaired renal or hepatic function in the last 12 months.
- The patient is currently using or has used cannabis or cannabinoid-based medications within 30 days of study entry and was unwilling to abstain for the duration of the study.
- Patients unwilling or unable to refrain from driving road vehicles and/or using potentially dangerous machinery where sufficient concentration is necessary.
- Patients unable to stay within the Netherlands for the duration of the study period.
- History of addiction and/or hospital admission due to addiction to recreational or pharmaceutical drugs.
- Patients with contradictions for MRI determined through the MRI safety form (see *K6\_Veilighedscontrole Proefpersonen*)

## 5. TREATMENT OF SUBJECTS

### 5.1 Investigational product/treatment

#### 5.1.1 Transvamix

The investigational medicinal product (IMP) is Transvamix, a cannabinoid-based medicine (CBM) comprising 100mg/mL THC (*delta-9-tetrahydrocannabinol*) and 50mg/mL CBD (*cannabidiol*) (*Transvamix-oil THC 10% / CBD 5%, 10ml*). Transvamix is prepared by Felix Farma B.V. using pharmaceutical-grade cannabis produced by Bedrocan B.V., and isolated using an ethanol-based extraction process. The end product, Transvamix, has a standardized cannabinoid composition within regulatory margins. Transvamix is administered using a 1ml syringe. (See *D2\_IMPD*).

#### 5.1.2 Placebo

The placebo formulation is comparable in texture, colour and taste. (see *D2\_IMPD* section 3.1)

### 5.2 Escape medication

Participants will continue analgesic and antipruritic treatments according to their current prescriptions and epidermolysis bullosa breakthrough pain guidelines – which include instructions for breakthrough symptoms. The IMP is not intended for breakthrough symptoms as participants will adhere to a strict dosing regimen. During the baseline visit participants will report all currently used systemic treatments. Participants will report changes in dosing or additional administration to these medications (for example for breakthrough medication) in the participant's logbook.

## 6. INVESTIGATIONAL PRODUCT

### 6.1 Name and description of investigational product(s)

TransvamiX THC 10% [100mg/mL] / CBD 5,0% [50mg/mL], 10 ml dark brown glass bottle with 1mL dosing syringe. (For more information see *D1\_Investigators Brochure*)

### 6.2 Summary of findings from non-clinical studies

Please see *D1\_Investigators Brochure* Chapter 4 (Nonclinical pharmacology and toxicology data)

### 6.3 Summary of findings from clinical studies

Please see *D1\_Investigators Brochure* Chapter 5 (Effects in humans)

### 6.4 Summary of known and potential risks and benefits

Sublingually administered TransvamiX-like drugs comprising THC and CBD are generally well tolerated. The most common treatment related adverse events are dizziness, nausea and fatigue.

Please see *D1\_Investigators Brochure* Chapter 5.2 (Safety and Efficacy).

### 6.5 Description and justification of route of administration and dosage

The choice of administration form for this study is via the sublingual oro-mucosal route. The lipid soluble cannabinoids administered in the form of an oil are readily absorbed through the mucosa into sublingual vessels. Pharmacokinetic studies have demonstrated the fast-onset plasma concentrations and ease-of-dosing of sublingually administered cannabinoids (tetrahydrocannabinol-THC & cannabidiol-CBD), compared to oral and intrapulmonary administration forms.

Although intrapulmonary administration (for example by way of vaporization) leads to faster peak plasma concentrations, the therapeutic effects are short-lived and the risk for side-effects is higher. Through the oral route (tablet/swallowed), due to its poor bio-availability and the hepatic first-pass metabolism, dosing is unpredictable with a higher inter-individual variability compared to sublingual and inhaled administration routes.

The current standard in both the clinical setting and research studies point to the need for step-wise dose titrations in patients receiving CBMs comprising THC and CBD. Patients administering TransvamiX and TransvamiX-like drugs, by way of the

sublingual/oromucosal route, perform a dose-escalation, following a premeditated titration scheme. The titration schemes used in clinical practice and research studies show variation in dose-escalation, the consensus however is to start with administration of the lowest dose possible, and escalate up to a maximum of 75mg THC per day, during 14 days. The scheme used in this study is designed by Felix Farma based on current recommendations for sublingually administered Transvamic-like drugs in the Netherlands.

In clinical practice this scheme is used as a reference for patients who may deviate from said doses, however for this study participants will adhere to the same dose-escalation scheme.

Taken together, the oromucosal route of administration appears to be the most patient-friendly which is supported by a recent Dutch study showing an epidemiologic preference for sublingual administration of CBMs versus oral and intrapulmonary.

## 6.6 Dosages, dosage modifications and method of administration

Transvamic and placebo are administered sublingually using a 1 millilitre dosing syringe. All participants will follow the predetermined titration scheme (*Table 2*). The titration will be stopped at the onset of side-effects (as reported by the participant), and the dose administered reduced by one day in the titration scheme. This will be called the sub-side effect threshold maintenance dose.

This achieved dose will be maintained for the remaining intervention period until day 14 is completed for each intervention (Transvamic and placebo). Both placebo and IMP (Transvamic) will undergo the same titration scheme.

The maximum dose is 0.75ml/day Transvamic or placebo (divided between 4 separate administrations).

For additional information please see *D1\_Investigators Brochure* chapter 5.3.1.

| Table 2: Titration Scheme                                 |           |          |           |            | Total   | Total THC | Total CBD |
|------------------------------------------------------------------|-----------|----------|-----------|------------|---------|-----------|-----------|
| Transvamic (100mg/mL THC & 50mg/mL CBD) & Placebo |           |          |           |            | (ml)    | (mg)      | (mg)      |
| Day                                                              | 6AM – 9AM | 11AM-2PM | 4PM – 7PM | 9PM – 12AM |         |           |           |
| 1                                                                | -         | -        | -         | 0,05 ml    | 0,05 ml | 5         | 2,5       |
| 2                                                                | -         | -        | -         | 0,05 ml    | 0,05 ml | 5         | 2,5       |
| 3                                                                | 0,05 ml   | -        | -         | 0,05 ml    | 0,1 ml  | 10        | 5         |
| 4                                                                | 0,05 ml   | -        | 0,05 ml   | 0,05 ml    | 0,15 ml | 15        | 7,5       |

|    |         |         |         |         |         |    |      |
|----|---------|---------|---------|---------|---------|----|------|
| 5  | 0,05 ml | 0,05 ml | 0,05 ml | 0,05 ml | 0,2 ml  | 20 | 10   |
| 6  | 0,05 ml | 0,05 ml | 0,05 ml | 0,1 ml  | 0,25 ml | 25 | 12,5 |
| 7  | 0,1 ml  | 0,05 ml | 0,05 ml | 0,1 ml  | 0,3 ml  | 30 | 15   |
| 8  | 0,1 ml  | 0,05 ml | 0,1 ml  | 0,1 ml  | 0,35 ml | 35 | 17,5 |
| 9  | 0,1 ml  | 0,1 ml  | 0,1 ml  | 0,1 ml  | 0,4 ml  | 40 | 20   |
| 10 | 0,1 ml  | 0,1 ml  | 0,1 ml  | 0,15 ml | 0,45 ml | 45 | 22,5 |
| 11 | 0,15 ml | 0,1 ml  | 0,1 ml  | 0,15 ml | 0,5 ml  | 50 | 25   |
| 12 | 0,15 ml | 0,1 ml  | 0,15 ml | 0,15 ml | 0,55 ml | 55 | 27,5 |
| 13 | 0,15 ml | 0,15 ml | 0,15 ml | 0,2 ml  | 0,65 ml | 65 | 32,5 |
| 14 | 0,2 ml  | 0,15 ml | 0,2 ml  | 0,2 ml  | 0,75 ml | 75 | 37,5 |

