### 8.3.1 Daily participant logbook completed by participants.

Participants will complete a logbook consisting of 3 parts each day in the evening (table 1) throughout the study period during which the participant received either Transvamic or placebo:

- Visual analog scales for pain and pruritus (VAS [no pain] 0-100 [worst pain/pruritus imaginable] units). These will be completed in the evening. Participants will be asked to complete VAS pain/pruritus retrospectively about the same day, subdivided into 3 timepoints in the day (*morning, afternoon and evening [or now]*).  
The periods of completion are as follows: Firstly, for baseline measurements (day -8 to -1) followed by Transvamic and placebo interventions (days 1 - 14 and 29 – 42).

- The titration scheme will be visualised and a checkbox ticked by the participant indicating the day of titration that was completed.
- Side effects will be reported following a multiple choice list\*, and the burden of the noted side effect indicated using numeric rating scales (NRS [not burdensome] 0-10 [extremely burdensome])
- Use of breakthrough medication or changes in analgesic medication recorded by participant.

\* Multiple choice list of side effects are categorized (in Dutch):

1. High gevoel (een vrolijke opgewekte stemming die langzaam overgaat in een tevreden gevoel van kalmte en rust).
2. Loomheid
3. Honger
4. Intensere beleving van kleuren en/of geluiden
5. Verlies van gevoel voor tijd en/of plaats
6. Sombere en/of angstige stemming
7. Rusteloosheid en/of slapeloosheid
8. Waanvoorstellingen
9. Versnelde hartslag
10. Duizeligheid
11. Warm of koud gevoel in handen en voeten
12. Rode branderige ogen
13. Spierverslapping
14. Droge mond
15. Anders, namelijk.....

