### **8.4 Withdrawal of individual subjects**

Subjects can leave the study at any time for any reason if they wish to do so without any consequences. The investigator can decide to withdraw a subject from the study for urgent medical reasons.

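### Section 6.6 answers every participant-reported side effect, delusions included, with a one-day step-back and dosing to day 14; no protocol section requires a hold or clinician decision before the next home dose

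*Protocol*

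**What the plan says.** Section 6.6 states the only dose modification for side effects: "The titration will be stopped at the onset of side-effects (as reported by the participant), and the dose administered reduced by one day" in Table 2. It continues: "This achieved dose will be maintained for the remaining intervention period until day 14 is completed for each intervention". It makes no distinction by type or severity. Section 6.5 accepts that patients in ordinary practice may deviate from the scheme, "however for this study participants will adhere to the same dose-escalation scheme".

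Section 8.3.1 defines what is reported and when. "Side effects will be reported following a multiple choice list", each with a 0-10 burden score. Item 8 is delusions ("8. Waanvoorstellingen"), on the same list as hunger and dry mouth. The timing is once a day: "Participants will complete a logbook consisting of 3 parts each day in the evening". No item carries an alert or an instruction to make contact.

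Other safeguards are present:
- Section 4.3 excludes "Patients with known psychotic disorder (including the use of antipsychotic medications), or a history of suicidal ideation".
- Section 8.4 lets participants leave at any time and adds: "The investigator can decide to withdraw a subject from the study for urgent medical reasons".
- Section 9.2.2 covers SAE reporting, 9.4 follow-up of all AEs, and 9.5 a DSMB that reviews adverse event data.
- Section 13.1j repeats the step-back and offers medical support in emergencies.

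Section 6.6 also refers to Investigator's Brochure chapter 5.3.1, which is not among the documents.

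**The concern.** A step-back that the participant carries out alone suits dizziness or a dry mouth. Delusions differ in kind, because they can impair the judgement on which a self-managed rule depends. The sponsor recognises psychosis as a risk at entry, yet the protocol has no matching rule on treatment.

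Dosing is at home, and Table 1 lists no clinic visit on days 1-13 or 30-41. Section 4.2 admits participants from age 16. Section 9.5 gives missing basic safety and tolerability data as its reason for a DSMB. A participant who reports delusions and follows 6.6 correctly goes on taking study drug, and no section requires a clinician to have judged the event first.

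**Working it through.** **Inputs.** Table 2 (section 6.6) gives the four daily administrations in ml. Section 5.1.1 gives 100 mg/mL THC. Days are titration days within a period; in the second period, study day = titration day + 28.

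**Reproducing the plan's figure.** Day 14: 0.2 + 0.15 + 0.2 + 0.2 = 0.75 ml; × 100 = 75 mg THC, as stated. All 14 rows reproduce. Daily THC for days 1-14 is 5, 5, 10, 15, 20, 25, 30, 35, 40, 45, 50, 55, 65 and 75 mg.

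**Cut in the daily total.** Cut = (dose on day d − dose on day d−1) / dose on day d.
- Day 1: no earlier step.
- Day 2: (5 − 5)/5 = 0%.
- Days 3-7: 50%, 33%, 25%, 20% and 17%.
- Days 8-13: see the table. Day 14 is left out because no dosing days follow it.

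| Onset day | Daily THC, onset → step-back | Cut in daily total | Administration that falls |
|---|---|---|---|
| 8 | 35 → 30 mg | 14.3% | 4PM-7PM, 0.1 → 0.05 ml (50%) |
| 9 | 40 → 35 mg | 12.5% | 11AM-2PM, 0.1 → 0.05 ml (50%) |
| 10 | 45 → 40 mg | 11.1% | 9PM-12AM, 0.15 → 0.1 ml (33%) |
| 11 | 50 → 45 mg | 10.0% | 6AM-9AM, 0.15 → 0.1 ml (33%) |
| 12 | 55 → 50 mg | 9.1% | 4PM-7PM, 0.15 → 0.1 ml (33%) |
| 13 | 65 → 55 mg | 15.4% | 11AM-2PM, 0.15 → 0.1 ml (33%); 9PM-12AM, 0.2 → 0.15 ml (25%) |

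Every administration not named in a row is unchanged. For example, suppose delusions begin after the 4PM-7PM dose on day 8 and the step-back applies at once. The next three doses (9PM-12AM 0.1 ml, 6AM-9AM 0.1 ml, 11AM-2PM 0.05 ml) are the same on the day 7 row as on the day 8 row. The first reduced dose is the fourth, the next day's 4PM-7PM.

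**What the rule does achieve.** THC over the remaining days is dose on day d−1 × (14 − d) under 6.6, against the sum of days d+1 to 14 under full titration.
- Onset day 4: 10 × 10 = 100 mg against 440 mg (77% less).
- Onset day 8: 30 × 6 = 180 mg against 40 + 45 + 50 + 55 + 65 + 75 = 330 mg (45% less).
- Onset day 12: 50 × 2 = 100 mg against 65 + 75 = 140 mg (29% less).

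**Timing.** Section 13.1j expects acute effects to be gone 4-8 hours after a dose. From day 5 there are four daily doses. The daytime windows are 5 hours apart at their midpoints and can be as little as 2 hours apart (9AM to 11AM). The next dose can therefore fall before the protocol expects the effect to have cleared.

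**Other sections.** Section 4.3 acts before dosing starts. Withdrawal by the investigator under 8.4 is optional and needs the investigator to know. Section 9.1 halts the whole study. Sections 9.2.2, 9.4 and 9.5 report, follow and monitor, with no stated consequence for one participant's next dose. Section 13.1j repeats the step-back.

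**Frequency.** The documents give none. Assuming a probability p per participant on Transvamix, the chance of at least one case in 16 is 1 − (1 − p)^16: 1.6% at p = 0.1%, 14.9% at 1% and 56.0% at 5%. Expected cases (16p) are 0.016, 0.16 and 0.8.

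**The case against.** The strongest reply is that 6.6 defines how a maintenance dose is found. Nothing in it overrides clinical management under 8.4, 9.2 or 9.4, participants may stop at any time, and section 13.2 describes a supervised, monitored setting. A reader might infer that the protocol orders dosing to continue through a psychiatric emergency, or that it has no safeguard. The documents do not support that: a clinician who knows of the event may act, and emergency support is promised. What stands is narrower. No section makes a hold or a decision mandatory before the next dose.

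A reader might also take the 9-15% to mean that the next dose is 85-91% of the one that preceded the delusions. That is wrong, because the figure compares daily totals. Each single administration is either unchanged or cut by 25-50%.

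It may be said that a logbook alert would be enough. It would not. The logbook is completed once, in the evening, so delusions after the morning dose could be followed by the midday and afternoon doses before anything is logged.

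Three limits remain. Investigator's Brochure 5.3.1 may already hold such a rule. The assumed frequency range is too wide to separate negligible from likely, so the case rests on severity. Confining the exception to item 8, and not extending it to low mood or rapid heartbeat, is a judgement; the reason is that delusions may impair the self-management that 6.6 relies on.

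**Conclusion.** The point holds as a gap in the dosing rule that should be closed. As written, 6.6 treats delusions like any minor side effect, and the protocol requires no hold or clinician decision before the next home dose. The rule does stop escalation. Measured against the dose at onset, though, the cut in daily THC is 9-15% for onset on days 8-13 and nil on day 2, with no lower step on day 1, and the next single dose may be unchanged.

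This rests on reading a one-day reduction as moving to the preceding row of Table 2, and on the protocol alone. Confidence is medium, mainly because Investigator's Brochure 5.3.1 is not shown.

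**What to change.** Amend 6.6 for delusions (8.3.1 item 8) only:
- At the start of each period, instruct the participant, or a household member, to stop study drug at once if delusions occur and to telephone the research clinician without waiting for the evening logbook.
- Keep dosing on hold until the clinician has documented a seriousness decision (9.2.2) and a decision either to resume at the step-back dose or to stop (8.4).
- As a backstop, add a RedCap alert and an on-screen hold message when item 8 is ticked.
- Apply the same rule in both periods, and still collect day 14 and day 42 outcomes.
- Keep the step-back for all other items.
- If Investigator's Brochure 5.3.1 already contains such a rule, state it in 6.6.

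The cost is a short amendment, one change to an existing form and a few calls by existing staff. A one-day hold after onset on day 8 omits 30 of the 180 mg THC otherwise due. A call about a psychotropic effect is a small unblinding cue in a 16-person crossover with a participant-reported primary outcome. Using the same trigger in both periods and keeping calls to safety content limits it.
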